## **6.6 SUBGROUP ANALYSES**

The following subgroup analyses will be performed to examine the consistency of treatment effects:

- Hepatitis C virus genotype subtype (1a, 1b)
- IL28B genotype (CC, CT, TT)
- Pretreatment cirrhotic status (cirrhotic, non-cirrhotic)

The proportion of patients with relapse of virologic response will be summarized by treatment group.

## **6.7 RESISTANCE ANALYSES**

Blood samples for resistance-monitoring studies will be taken according to the Schedule of Assessments (see [Appendix A](#)). Patients' samples for resistance-monitoring studies will be selected on the basis of results obtained from the COBAS TaqMan HCV v2.0 test.

Resistance-monitoring studies will be performed as detailed in [Section 4.5.1.8](#).

The genotype of boceprevir- and/or RO5024048-resistant samples (defined as those samples for which  $FC \geq 3$ ) will be determined through population sequencing of the NS5B coding region.

The quotient of antiviral  $IC_{50}$  values determined in the mutant and in the wild-type replicons will be determined as FC values to describe the level of resistance to RO5024048 and/or boceprevir.

Samples (encompassing the NS3 protease, NS5B polymerase, and/or other regions of the HCV genome) may also be used to test for resistance to other small antiviral molecules. Sampling procedures, storage conditions, and shipment instructions will be provided in a supplemental laboratory manual.

The findings from these analyses will be listed for each patient selected for these analyses. Data will be reported following the FDA guidelines for the reporting of drug-resistance data.

The rate of resistance will be summarized by treatment group.

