### **1.2.2      HCV Protease Inhibitor (Boceprevir)**

Boceprevir is a structurally novel peptidomimetic ketoamide protease inhibitor that binds reversibly to the HCV non-structural 3 (NS3) active site, inhibiting viral replication. Boceprevir is mainly metabolized by the aldo-keto reductase (AKR) pathway and also undergoes oxidative metabolism by cytochrome P450 (CYP) 3A4/5, making boceprevir a potent CYP3A4/5 inhibitor (Ghosal et al. 2011).

Based on available information, the findings identified in general toxicology studies with boceprevir include neutrophil infiltrates in the liver of mice and multinucleated hepatocytes in rats. Testicular degeneration was observed in male rats, but not in male mice or monkeys. These findings are considered species specific in nature and occur at exposures that are slightly higher than or similar to the intended clinical therapeutic dose. Increases in activated partial thromboplastin time (aPTT) have been observed in monkey toxicity studies; in the absence, however, of gross pathology evidence of hemorrhage. Based on preclinical toxicity profile for boceprevir, no overlapping target organ of toxicity with RO5024048 is expected.

Boceprevir is not expected to affect the pharmacokinetics of RO5024048 or vice versa. Boceprevir has been identified in vitro as an inhibitor of CYP3A and P-glycoprotein (P-gp); however, RO5024048 is not metabolized by CYP3A and is not a P-gp substrate. RO5024048 and RO4995855 (parent) did not show any relevant in vitro CYP inhibition or induction (RO4995855 only) potential that may affect boceprevir. RO5024048 has not been assessed as an inhibitor of AKRs, the major boceprevir metabolizing enzyme. However, because of the ubiquitous nature of AKRs and the lack of clinical interaction shown in a drug–drug interaction study with boceprevir using an AKR inhibitor, a drug–drug interaction is very unlikely (Boceprevir IB 2012).

A Phase I study comparing boceprevir monotherapy, PegIntron® monotherapy, and boceprevir plus PegIntron combination therapy in genotype 1 patients who failed previous treatment with PegIntron with or without RBV showed that combination therapy with boceprevir and PegIntron produced greater reductions in viral load than either drug given as monotherapy (Berman et al. 2009; Sarrazin et al. 2007).

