#### **4.5.1.8 Hepatitis C Virus Drug-Resistance Monitoring**

Blood samples will be collected throughout the study as detailed in the Schedule of Assessments (see [Appendix A](#)) to monitor for the development of drug resistance.

During the course of the study, phenotypic and/or sequence analyses will be performed on samples from patients who experience virologic breakthrough, partial response, non-response, relapse, and phenotypic analysis at baseline for approximately 5% of patients who maintain response through follow up. To prevent prolonged dosing in the event of a virologic breakthrough or partial response after one single measurement of HCV RNA breakthrough, a confirmatory sample should be drawn within 2 weeks. To confirm a relapse after one single measurement of HCV RNA relapse, another sample should be drawn within 2 weeks.

Patients who develop resistance to RO5024048 and/or to boceprevir while on RO5024048 and boceprevir treatment will be monitored for the persistence of RO5024048- and/or boceprevir-resistant mutation(s) during the follow-up period.

Population sequencing of the complete coding sequence of the HCV NS3/4A and/or NS3 protease and NS5B (for boceprevir- and RO5024048-containing cohorts) of all baseline samples (Day 1) will be performed using standard sequencing technology.

Patients with evidence of a partial response or virologic breakthrough (in the presence or absence of confirmed resistance) will be asked to participate in a separate Roche study for resistance monitoring (Study NV22688), where sequence analysis will be performed. For these patients, samples will be collected and analyzed as detailed in the protocol. For those patients where resistance is not confirmed, samples will be taken for future analyses in case a new resistance mutation to RO5024048 is identified. Clonal and/or ultradeep sequencing and/or phenotypic analysis may also be performed on these samples.

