## Patient Identification for Resistance Analysis

Samples will be selected for sequence determination of the NS3 protease and NS5B coding region(s) from patients experiencing (for the purposes of sequence determination an HCV RNA  $\geq 1000$  IU/mL is required):

1. Virologic breakthrough
  - a) Those patients who show either a sustained increase in HCV RNA of  $\geq 1 \log_{10}$  IU/mL ( $\geq 2$  consecutive measurements) while on boceprevir/RO5024048 compared with the on-treatment nadir (where the nadir was a  $\geq 1 \log_{10}$  IU/mL decrease from baseline after 2 weeks of treatment)
  - b) Those patients with confirmed quantifiable HCV RNA ( $\geq 25$  IU/mL by  $\geq 2$  consecutive measurements) in a patient who had been previously confirmed as having unquantifiable HCV RNA ( $< 25$  IU/mL by  $\geq 2$  consecutive measurements) before the end of boceprevir/RO5024048 treatment
  - c) Those patients who responded ( $< 25$  IU/mL by  $\geq 2$  consecutive measurements) to boceprevir/RO5024048 treatment and who have subsequent quantifiable viral load ( $\geq 25$  IU/mL by  $\geq 2$  consecutive measurements) once boceprevir/RO5024048 treatment has been completed (but Pegasys/Copegus treatment continues).
2. Partial response. Those patients who show an initial HCV RNA decline (a  $\geq 1 \log_{10}$  IU/mL decrease from baseline after 2 weeks of treatment) followed by stabilization ( $\geq 2$  consecutive measurements similar to those at nadir) while on boceprevir/RO5024048 treatment and/or experience a HCV RNA  $\geq 1000$  IU/mL by the end of boceprevir/RO5024048 treatment of at least 4 weeks in duration
3. Non-response. A decrease in HCV RNA of  $< 1 \log_{10}$  IU/mL from baseline after 2 weeks of treatment
4. Relapse. Patients who responded to boceprevir/RO5024048 treatment and have subsequent quantifiable viral load ( $\geq 25$  IU/mL by  $\geq 2$  consecutive measurements) once all treatment has been completed.

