## Sample Selection, Clonal Sequence, and Phenotypic Analyses

The following samples from patients identified in Section 4.5.1.8 will be selected for sequence determination of the NS3 protease and/or NS5B coding sequences (if HCV RNA  $\geq 1000$  IU/mL).

1. Baseline sample (Day 1 before initiation of treatment) for patients with HCV RNA breakthrough, partial response, non-response, and relapse
2. First sample after nadir that shows HCV RNA  $> 1000$  IU/mL for patients who experience HCV RNA breakthrough while on boceprevir/RO5024048 treatment (or subsequent samples if amplification fails)

3. Additional samples collected after breakthrough, but before the end of boceprevir/RO5024048 treatment may be assessed, particularly if viral complementary DNA (cDNA) amplification from the first sample after nadir failed for patients with HCV RNA breakthrough
4. End-of-boceprevir/RO5024048 treatment sample from patients who experience partial response while on boceprevir/RO5024048 treatment
5. First sample after quantifiable viral load (or later samples if HCV RNA is higher and allows amplification) that shows HCV RNA > 1000 IU/mL for patients who experience sustained HCV RNA relapse once study drug treatment has been completed

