### **Clonal Sequence Analyses**

Clonal sequence analysis will be performed if a population-based sequence of on-treatment samples (or PK data) cannot explain an HCV RNA breakthrough, partial response, or non-response and will be performed on the on-treatment and baseline samples previously analyzed through population sequence.

Clonal sequence analysis will be performed on on-treatment samples from patients with mixtures of amino acid substitutions at positions known to confer resistance to boceprevir or RO5024048 that develop during therapy. This analysis will assist in the understanding of the percentage of mutant/wild-type variants within a patient's quasispecies.

For patients who experienced virologic failure clearly associated with the emergence of a boceprevir and/or RO5024048 resistance-associated substitution(s) and for the analysis of the last sample for resistance testing in Study NV27780 (to assess the persistence of the resistance mutation[s]), population sequence will be used as the primary methodology for the detection of a previously detected resistance mutation(s). Should such mutation(s) not be detected by population sequence, a clonal-based method ( $\geq 80$  clones/sample or equivalent) will be used to assess the patient's eligibility for enrollment in Study NV22688.

Sequence variations of the samples after HCV RNA breakthrough or partial response will be determined and compared with the baseline sequences of the samples from each selected patient and with the corresponding subtype reference sequence.

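### Section 6.7 genotypes boceprevir-resistant samples in NS5B only, and the Section 4.5.1.8 sample lists name no on-treatment sample for non-responders

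*Protocol*

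**What the plan says.** Section 6.7 (Resistance Analyses) calls a sample resistant when its fold change is at least 3. It states that the genotype of samples resistant to boceprevir and/or RO5024048 "will be determined through population sequencing of the NS5B coding region". Just before that it says that "Resistance-monitoring studies will be performed as detailed in" Section 4.5.1.8, and it ends by promising a resistance rate for each treatment group.

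Section 1.2.2 says that boceprevir "binds reversibly to the HCV non-structural 3 (NS3) active site"; Section 1.2.1 describes RO5024048 as an NS5B polymerase inhibitor.

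Section 4.5.1.8 covers both regions:

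- For all Day 1 samples it plans "Population sequencing of the complete coding sequence of the HCV NS3/4A and/or NS3 protease and NS5B".
- For virologic failures it says: "Samples will be selected for sequence determination of the NS3 protease and NS5B coding region(s) from patients experiencing" one of four outcomes, the third of which is non-response (a fall of less than 1 log10 IU/mL after 2 weeks).
- The selected samples "will be selected for sequence determination of the NS3 protease and/or NS5B coding sequences", provided HCV RNA is at least 1000 IU/mL.

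In the numbered list that follows, non-response appears only in item 1, the baseline sample. Later items cover the other outcomes, for example "End-of-boceprevir/RO5024048 treatment sample from patients who experience partial response while on boceprevir/RO5024048 treatment". The clonal paragraph then calls for clonal sequencing when the population sequence of on-treatment samples, or the PK data, "cannot explain an HCV RNA breakthrough, partial response, or non-response". It applies this to on-treatment and baseline samples that have already been population-sequenced.

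**The concern.** There are two separate faults.

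First, the analysis section names boceprevir and then prescribes sequencing of the other drug's target. Two analysts could defensibly prepare different genotype tables for boceprevir, one from the Section 6.7 sentence and one from Section 4.5.1.8.

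Second, emergent resistance is shown by comparing an on-treatment sample with baseline. If only the baseline sample of a non-responder is sequenced and phenotyped, that patient cannot contribute an emergent resistance event, whatever virus is present on treatment.

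Documented resistance is a secondary outcome (Section 3.4.1.2), and estimating the proportion who develop it is a secondary objective (Section 2.2). An anticipated drop in treatment-emergent boceprevir resistance is also one of the two reasons given in Section 6.1 for expecting an SVR of 45% to 55%. The boceprevir genotypes and the resistance rate should therefore be defined without ambiguity.

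**Working it through.** The protocol states no figure for resistance or non-response, so there is none to reproduce. The check is a comparison of the text, with a simple scale at the end.

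**1. Region sequenced**

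| Place | Samples | Region |
|---|---|---|
| 4.5.1.8, opening text | all Day 1 samples | NS3/4A and/or NS3, and NS5B |
| 4.5.1.8, patient identification | virologic failures | NS3 and NS5B |
| 4.5.1.8, sample selection | selected samples | NS3 and/or NS5B |
| 4.5.1.8, phenotyping | selected samples | NS3 and/or NS5B |
| 6.7 | resistant to either drug, fold change ≥ 3 | NS5B only |

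Section 6.7 is the only place that omits NS3. Its sentence applies to samples already classed as resistant by fold change, so it governs how they are described and not whether they are found.

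**2. Post-baseline samples by outcome**

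| Outcome | Sequencing list | Phenotyping list |
|---|---|---|
| Breakthrough | items 2, 3 | items 2, 3, 5 |
| Partial response | item 4 | item 4 |
| Relapse | item 5 | item 6 |
| Non-response | none | none |

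The on-treatment sequence that the clonal paragraph presupposes for non-response is created by no item. Because the phenotyping list has the same gap, fold change does not fill it.

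**3. Which non-responders reach a list by another route**

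Take a patient with a fall of less than 1 log10 at Week 2.

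- Breakthrough, limb (a), needs a nadir at least 1 log10 below baseline after 2 weeks. On a plain reading it is not met.
- Breakthrough, limbs (b) and (c), and relapse need an earlier response. A late responder who then fails can qualify.
- Partial response, first limb, needs the initial 1 log10 fall and is not met. The second limb, HCV RNA ≥ 1000 IU/mL at the end of at least 4 weeks of treatment with the two antivirals, can be met if its *and/or* is read as standing alone.

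On that reading, the patients left without a named post-baseline sample are mainly those who stop both antivirals before 4 weeks, or who end below 1000 IU/mL without a confirmed response. If the second limb is read as still requiring the initial fall, every non-responder who never responds is left out.

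**4. Is there a sample to sequence?**

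Appendix A schedules a resistance sample at baseline and at every treatment visit, including Week 2. Entry requires HCV RNA ≥ 50,000 IU/mL. If the Day 1 value is also at least that, a fall of less than 1 log10 leaves more than 50,000 / 10 = 5,000 IU/mL at Week 2, which is above the 1000 IU/mL threshold.

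**5. Scale**

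With 30 patients per group, k missed patients lower the observed rate by k/30. The values of k are assumptions:

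| k | Loss (percentage points) |
|---|---|
| 0 | 0 |
| 1 | 3.3 |
| 2 | 6.7 |
| 3 | 10.0 |

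**6. Potency measure**

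Section 4.5.1.8 forms fold change from EC50 values and Section 6.7 from IC50 values.

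**The case against.** The best defence is that Section 6.7 defers to Section 4.5.1.8, which sequences and phenotypes NS3 throughout, so the NS3 data will exist. That stands. A reader might infer from the NS5B sentence that reported boceprevir resistance would be zero by construction, or that the sentence biases the resistance rate downward. The documents do not support either: the sentence starts from samples already called resistant by fold change, and susceptibility to boceprevir is tested separately. What the defence leaves is a specific rule that is wrong for one of the two drugs, placed directly after the general cross-reference.

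On non-responders, a reader might infer that all emergent resistance in anyone with less than a 1 log10 fall at Week 2 would go unseen. That is also too strong. The opening of Section 4.5.1.8 includes non-response among the outcomes to be analysed, the patient-identification list has it as a category, and site-directed mutagenesis extends to variations in treated non-responders. No rule in Section 4.6.1.1 stops treatment for a Week 2 non-response as such, so many of these patients could later meet another definition. The intent is clear, but the two lists that decide which samples are processed do not carry it out.

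It is also fair that this is an exploratory trial without hypothesis tests, that SVR-12 is untouched, and that the EC50/IC50 difference is a matter of labelling with no shown effect on a result.

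**Conclusion.** The point holds in a limited form. Section 6.7 is wrong for boceprevir and conflicts with Section 4.5.1.8; the consequence is a missing or ambiguous NS3 genotype for samples already known to be resistant, not missed resistance. The lists in Section 4.5.1.8 omit the on-treatment sample that the same section presupposes for non-responders; the consequence is possible undercounting among those who meet no other failure definition.

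The size of that undercount is unknown and may be zero. It depends on how many patients are non-responders, how the partial-response definition is read, and how many of those left over carry emergent resistance. None of these is given. The 3.3 points per missed patient assumes a denominator of 30 per group. This is a minor to moderate correction to a descriptive secondary endpoint and does not affect the primary analysis.

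**What to change.** 1. In Section 6.7, replace the NS5B phrase with: *population sequencing of the NS3/4A protease region (boceprevir) and the NS5B region (RO5024048)*.
2. In both the sequencing and the phenotyping list of Section 4.5.1.8, add: *last on-treatment sample with HCV RNA ≥ 1000 IU/mL for patients with non-response*.
3. Name one potency measure for fold change and use it in both sections.

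The cost is a few lines of text, plus sequencing and phenotyping of a small number of samples. No new blood draw is needed, because Appendix A already collects resistance samples at every visit from baseline on.

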## **6.8 PHARMACOKINETIC ANALYSES**

Data may be combined with those from other studies for population PK analyses using non-linear mixed effects modeling to describe the time course of the plasma concentrations of RO4995855. The influence of demographic covariates (such as body weight, age, and sex) on RO4995855 PK parameters (i.e., clearance and volume of distribution) will be investigated if appropriate.

## **6.9 EXPLORATORY ANALYSES**

An exploratory analysis will be performed to assess the PD response and emergence of resistance. Graphical and statistical techniques such as linear, non-linear, and logistic regression will be used to explore potential relationships between treatment regimen, PK, viral, and host factors and safety and efficacy parameters.

### **6.9.1      Biomarker Analyses**

Biomarker analyses will explore the impact of baseline IP-10 on treatment response. The analyses will be exploratory and will not be part of the final Clinical Study Report. Analysis will be completed as appropriate. Details of the exploratory analyses will be provided in a separate SAP.

### **6.10      INTERIM ANALYSES**

At least one interim analysis of efficacy and safety data will be performed to inform the RO5024048 clinical development plan. An interim analysis will be performed for safety after all patients complete Week 12, and for safety and efficacy after all patients complete Week 36 and potentially at other timepoints as needed. Virologic response with a confidence interval will be summarized by visit. Presentations of resistance rates and of safety data including tabulations of all AEs, all laboratory abnormalities, and reasons for dose modifications and/or discontinuation from trial medications will be prepared.

## **7.      DATA COLLECTION AND MANAGEMENT**

### **7.1      DATA QUALITY ASSURANCE**

Roche will be responsible for data management of this study, including quality checking of the data. Data entered manually will be collected via EDC using eCRFs. Sites will be responsible for data entry into the EDC system. In the event of discrepant data, Roche will request data clarification from the sites. The sites will resolve discrepant data electronically in the EDC system.

Roche will produce an EDC Study Specification document that describes the quality checking to be performed on the data. Central laboratory data will be sent directly to Roche, using Roche's standard procedures to handle and process the electronic transfer of these data.

Electronic CRFs and correction documentation will be maintained in the EDC system's audit trail. System backups for data stored at Roche and records retention for the study data will be consistent with Roche's standard procedures.

### **7.2      ELECTRONIC CASE REPORT FORMS**

Electronic CRFs are to be completed using a Sponsor-designated EDC system. Sites will receive training and have access to a manual for appropriate eCRF completion. Electronic CRFs will be submitted electronically to Roche and should be handled in accordance with instructions from Roche.

All eCRFs should be completed by designated, trained site staff. Electronic CRFs should be reviewed and electronically signed and dated by the investigator or a designee.

At the end of the study, the investigator will receive patient data for his or her site in a readable format on a compact disc that must be kept with the study records. Acknowledgement of receipt of the compact disc is required.

### **7.3 SOURCE DATA DOCUMENTATION**

Study monitors will perform ongoing source data verification to confirm that critical protocol data (i.e., source data) entered into the eCRFs by authorized site personnel are accurate, complete, and verifiable from source documents.

Source documents (paper or electronic) are those in which patient data are recorded and documented for the first time. They include, but are not limited to, hospital records, clinical and office charts, laboratory notes, memoranda, patient-reported outcomes, evaluation checklists, pharmacy dispensing records, recorded data from automated instruments, copies of transcriptions that are certified after verification as being accurate and complete, microfiche, photographic negatives, microfilm or magnetic media, X-rays, patient files, and records kept at pharmacies, laboratories, and medicotechnical departments involved in a clinical trial.

Before study initiation, the types of source documents that are to be generated will be clearly defined in the Trial Monitoring Plan. This includes any protocol data to be entered directly into the eCRFs (i.e., no prior written or electronic record of the data) and considered source data.

Source documents that are required to verify the validity and completeness of data entered into the eCRFs must not be obliterated or destroyed and must be retained per the policy for retention of records described in Section 7.5.

To facilitate source data verification, the investigators and institutions must provide the Sponsor direct access to applicable source documents and reports for trial-related monitoring, Sponsor audits, and IRB/EC review. The investigational site must also allow inspection by applicable health authorities.

